**Antimicrobial therapy for infectious illness**

The standard antimicrobial therapy for management of severely malnourished children at the Dhaka hospital of ICDDR,B will be used for management of the study children.

Pneumonia: children will receive parenteral chloramphenicol in a dose of 75-100 mg/kg.day in 4 equally divided doses for the first 2 days followed by an oral formulation in the same dosage for the next 5 days.

If no clinical improvement is observed to occur within 48 hours (i.e. patients remain febrile and or respiratory rate does not come down) or if the clinical condition deteriorates after 24 hours of treatment, chloramphenicol will be replaced by parenteral ceftriaxone to be administered in a dose of 100mg/kg once daily plus gentamicin 1.5 mg/kg parenterally every 8 hours for 7 to 10 days.

Diarrhoea: Children with cholera will be treated with erythromycin administered in a dose of 12.5 mg/kg body weight every 6 hours for 3 days, and those with shigellosis will be treated with 12.5 mg/kg of pivmecillinan every 6 hours for five days.

**Micronutrients**

The following vitamins and minerals are routinely provided to severely malnourished children admitted to the Dhaka hospital of ICDDR,B: elemental zinc and folic acid are administered in a dose of 2 mg/kg and 1.25 mg/day respectively for 15 days; magnesium sulfate is administered in a dose of 0.4 mmol/kg as an intramuscular injection once a day for seven days. Multivitamin (MV) drops are provided in a dose of 1 ml daily. One millilitre of commercially available MV drops contains vitamin A (as palmitate) 5,000 IU, vitamin D 1,000 IU, thiamine hydrochloride 1.6 mg, riboflavin 1 mg, pyridoxine hydrochloride 1 mg, nicotinamide 10 mg, calcium D-pantothenate 5 mg, and ascorbic acid 50 mg.

**Management of associated conditions**

1. Hypoglycemia (blood glucose <3mmol/L or 54mg/L, measured by Dextrostix): Patients with symptomatic hypoglycemia, presenting with unconsciousness or convulsions, would be given 2ml/kg of 25% glucose immediately through intravenous route followed by 10% glucose orally or by nasogastric tube (for patients who are unable to drink due to reasons such as unconsciousness, weakness or frequent vomiting) for prevention or recurrence of hypoglycemia.
2. Hypokalaemia (serum potassium of < 3.5mmol/L) [60]: Manifestations of hypokalaemia are usually evident with a serum potassium concentration of 2.5mEq/L or below [61]. Children may require intravenous infusion due to severe dehydration. In that case, if serum potassium is <2.0 mmol/L potassium chloride will be added to infusion to raise the potassium concentration to 40 mmol/L, and if serum potassium is between 2 to 2.5 mmol/L, potassium in the infusion solution would be increased to 30mmol/L. Oral potassium chloride, 4 mmol/kg.day (5 ml syrup containing 7 mmol of elemental potassium), will be supplemented 3 times/day for 5 days to children without manifestation of hypokalaemia.
3. Thrush (oral candidiasis): Nystatin oral drops 1 ml (100,000 units) will be given 4 times daily for 5 days or until cure.
4. Specific infections: Will be treated with appropriate antimicrobial, as determined by susceptibility report.
5. Complications: During acute phase treatment, complications will be managed according to cause.
6. Diet: For children presenting with dehydration, feeding will be started as soon as rehydration is accomplished or as soon as possible after admission. Diet would be given in the form of 10 ml/ kg every 2 hour of milk suji, which provides 67 kcal/100ml of energy, by nasogastric tube (to ensure intake by patients with poor appetite, repeated vomiting, weakness and painful oral lesion e.g. stomatitis/glossitis/gingivitis) until they are able to resume oral feeding. In addition, semisolid foods and milk suji 100 (high energy milk-based therapeutic diet) would be given to the children when they enter the nutritional rehabilitation phase. The management of this phase is based on a standardized dietary protocol which is routinely followed in the Nutritional Rehabilitation Unit (NRU) of the hospital.
7. **Outcome variables**

**Primary outcome**

1. Resolution of diarrhoea
2. Resolution of ALRI

**Secondary outcomes**

1. Duration of acute phase of illness
2. Time to nutritional rehabilitation (achieving of 80% of W/H)
3. Rates of weight gain
4. Morbidity developed during hospitalization such as nosocomial infections
5. Serum retinol and RBP on admission and on day 15
6. Case fatality rates

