**Specific Aims:**

Describe the specific aims of the proposed study. State the specific parameters, biological functions/ rates/ processes that will be assessed by specific methods **(TYPE WITHIN LIMITS).**

Primary aim

To compare the proportion of severely malnourished, hospitalized children, aged 5-59 months, experiencing resolution of diarrhoea and ALRI/pneumonia in association with a single mega dose (200,000 IU) followed by daily low dose (5,000 IU) of vitamin versus daily low dose (5,000 IU) of vitamin A as an adjunct to standard management of their primary illnesses.

Secondary aims: The secondary aims of the study are to compare:

1. Duration of hospital stay, and the rates of weight gain more than 10 gm/kg/day among children in the two intervention groups.
2. Case-fatality among children in the two intervention groups, and
3. Serum retinol and retinol binding protein (RBP) levels on admission, day 3 and on day 15.

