The reports on mortality and morbidity of diarrhoea and pneumonia in severely malnourished children associated with vitamin A supplementation are also conflicting. Some studies have observed no significant difference in mortality (8% vs. 8.4%) or in hospital stay (10 days vs. 9 days) in high and low dose groups respectively [13].However, in sub-group analysis significantly lower deaths was observed among oedematous children who received low dose vitamin A on admission [38].

A meta-analysis observed substantial reduction in mortality in association with vitamin A supplementation in population where at least low-level deficiency state was prevalent, and the effect was independent of dose, sex, and age, and the effect was more pronounced for incidence of diarrhoea than for respiratory diseases [39]. However, no difference in morbidity (frequency, duration, or prevalence) from diarrhoeal or respiratory diseases was noted (Ghana VAST Study Team) [40] among stunted children in Ghana.

Malnourished children are deficient in retinol binding protein (RBP) and thus the resultant free, unbound form of vitamin A is excreted either through urine or faces, and the situation is aggravated in acute infections. Vitamin A, when administered in a single high dose, presumably circulates in free form in the extra cellular fluids before being taken up by the liver. This free form of vitamin A perhaps affects sodium and water metabolism causing ‘pseudotumor cerebri’, an adverse event of hypervitaminosis A [41]. Lack of adequate food is an important cause of malnutrition, and the bioavailability of vitamin A from the consumed plant and meat source is also low **(**Dietary Reference Intakes for Vitamin A. <http://www.nap.edu/openbook/0309072794/html/ 6.5.html. Accessed> May 20, 2005 at 1400 hrs). A national nutritional survey in Bangladesh [42] observed vitamin A deficiency as a significant public health problem in various population groups. Although the prevalence of clinical signs of vitamin A deficiency greatly reduced from 3.6% in 1982-83 to 0.6% in 1996 in Bangladesh, the prevalence of sub-clinical vitamin A deficiency among the preschool children remained higher in a hospital based study with small sample size [42].

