**Study design**

This will be a randomized, double blind, controlled clinical trial examining the effects of daily low dose versus single large dose followed by daily low dose of vitamin A supplementation on the diarrhoea and ALRI/pneumonia morbidities of severely malnourished hospitalized children.

Study site

The study will be conducted at the Dhaka hospital of ICDDR, B. The hospital is located in Dhaka, the capital city of Bangladesh that has a population of over 13 million. Each year, around 100,000 diarrhoeal patients, with and without complications, attend the hospital seeking treatment for their illnesses, and about 6000 of them, mostly under-five children, require admission to the longer stay wards for complications of diarrhoea or presence of other infectious diseases, particularly ALRI/pneumonia and sepsis, and severe malnutrition (45 to 50%).

Inclusion criteria

1. Age 6-59 months
2. Either sex
3. Severe malnutrition as defined by the presence of any of the followings:
   1. Bipedal oedema
   2. Weight (measured after correction of dehydration) for height Z score <-3 of the National Center for Health Statistics (NCHS) reference
   3. Written informed consent of respective parents/ guardians for participation of the children in the study.

Exclusion criteria

1. Failure to obtain consent
2. Received a dose of vitamin A within the last three months
3. History of night blindness or eye signs of vitamin A deficiency
4. Measles or history of measles within last 8 weeks [49]
5. Clinical suspicion of TB (evening rise of temperature, loss of appetite, gradual loss of weight, cough, night sweating) after applying modified Kenneth Jones criteria [50], shock other than due to hypovolaemia or hypoglycaemia, congestive cardiac failure, severe sepsis (hypothermia, tachycardia, tachypnea, hypotension) [51], and seizures disorders
6. Trisomy-21
7. Cerebral palsy
8. Any other known chronic disease (eg. hepatic, renal or congenital disorder) or malignant condition.

Final inclusion in the study

Dehydration would be assessed using a modified WHO guidelines (Dhaka Method)[52] that is routinely practiced at the hospital. Dehydration would be managed using oral or intravenous fluids, as appropriate, following the WHO guidelines. A final diagnosis of acute infection, either diarrhoea or ALRI/pneumonia or both, will be made after the correction of dehydration and patient will be enrolled in the study.

Study Interventions

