   1. Children will be screened for recruitment between 9 am to 4 pm everyday. A trained research assistant will initially screen them. After explaining the study including its aims, procedures, interventions and their possible risks and benefits, rights to refuse participation and withdrawal of consent during study, and confidential handling of information the parents/guardians would require to give consent to enroll their children. The same research assistant will then perform anthropometric measurements including height, weight and mid upper arm circumference, and calculate weight for age, height for age and weight for height percentiles taking National Center for Health Statistics (NCHS) median as the standard. Z-scores will be computed and children with weight for height Z-score less than 3 will be enrolled in the study .
   2. Final enrollment: After rehydration, children will be re-weighed, and final enrollment will be done if weight for height Z-score less than 3 .
2. **Clinical Assessments**
   1. Research assistant will collect the demographic and other data using a pre-designed clinical record form (CRF).
   2. One of the investigators will obtain pertinent medical history and perform through physical examination, and also ensure that the children meet eligibility criteria. All information would be recorded on a pre-designed and pre-tested case report form (CRF).
   3. Randomization: Patient will be randomly assigned to either of the two interventions based on a computer generated randomization table.
   4. During hospitalization data will be collected on the outcome variables as well as relevant clinical information including type and severity of diarrhoea and pneumonia.
   5. All the patients will receive standard treatment as per the hospital’s guidelines.
3. Laboratory assays
   1. **Blood test**s: Blood for retinol and RBP, glucose, complete blood count, serum electrolytes, total protein, albumin and, as measures of infection status, pre-albumin and C-reactive protein (CRP) will be measured after randomization on the admission day. Serum retinol and RBP will also be measured on study day-3 and 15. Any other heamatological test will be repeated if only clinically indicated. . Approximately 3.0 ml of venous blood will be adequate to perform all of the tests.

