One of the investigators will assess study children at least once daily, usually in the morning; however, additional assessments may be performed in the interim if deemed necessary for clinical management. Each child will be weighed every morning, without clothes, to the nearest 0.5 gm using an electronic weighing scale (model 6810; Seca Corporation, Columbia, MD). Height, or recumbent length in children less than 2 years of age, will be measured with a standard height or length board to the nearest 0.1centimeter. MUAC will be measured midpoint between the elbow and the shoulder of the left arm with a non-expanding tape and recorded to the nearest 0.1 cm. Rectal temperatures will be measured 3 times/ day.

1. Morbidity evaluation

Morbidity data such as presence of cough, difficult breathing, fever and other symptoms, and findings of physical examination including pulse and respiratory rates, presence of oedema, mental status (lethargy, irritable, drowsy, obtundation, coma), dehydration status, lower chest wall in-drawing will be recorded. Detailed inquiries will be made about stool frequency, consistency and contents (mucus, blood, undigested food etc).

1. **Discharge from the hospital**: Patients will be discharged after recovery.
2. Definition of recovery from acute phase illness

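### The 80% weight-for-height endpoint carries no oedema condition, although bipedal oedema alone qualifies a child for entry

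*Protocol*

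**What the plan says.** - **Entry.** The Inclusion criteria give "Severe malnutrition as defined by the presence of any of the followings" and list two alternatives: "Bipedal oedema", with no limit on weight-for-height, and "Weight (measured after correction of dehydration) for height Z score <-3". Dehydration is the only fluid disturbance for which weight is corrected.
- **Final enrolment.** Under Patient recruitment the rule is different: "After rehydration, children will be re-weighed, and final enrollment will be done if weight for height Z-score less than 3" (a minus sign appears to have been lost in extraction). Oedema is not mentioned there.
- **Endpoints.** Secondary outcomes include "Time to nutritional rehabilitation (achieving of 80% of W/H" and, separately, rates of weight gain. The Specific Aims put a threshold on the latter: "Duration of hospital stay, and the rates of weight gain more than 10 gm/kg/day among children in the two intervention groups". Neither place gives a start weight, a start day or an observation window for weight gain.
- **Measurement.** Under Daily examination and recordings, "Each child will be weighed every morning, without clothes". Under Morbidity evaluation, presence of oedema is recorded as a physical sign. Nothing links it to either weight outcome.

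**The concern.** Oedema is excess body water, and it adds to the weight on the scale. The protocol treats it as sufficient evidence of severe malnutrition at entry, then defines rehabilitation by a weight ratio that the same fluid inflates. A child can therefore satisfy the rehabilitation endpoint and the entry definition of severe malnutrition on the same day. An event at entry comes before the treatment could act, so it says nothing about dose and dilutes the time-to-event comparison.

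Weight gain has the opposite problem. If it is counted from an oedematous admission weight, losing the fluid is an improvement but subtracts from the measured gain, and the child may miss the 10 g/kg/day threshold because of recovery.

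At stake are two secondary outcomes, in a subgroup whose mortality result in earlier work the Project Summary says needs further examination. The primary outcomes are not affected.

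**Working it through.** The protocol gives no figure for this point. Its one calculation is the sample size, which rests on 48-hour clinical success: (0.70 x 0.30 + 0.85 x 0.15) x 7.84 / 0.15² = 117.6, which reproduces the stated 118 per group. It does not bear on the weight outcomes.

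**Assumption.** Oedema fluid is a fraction f of admission weight. The documents give no value, so f = 5%, 10% and 15% are shown. The share of oedematous children is also not given.

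**1. Weight-for-height at entry.** Scale W/H = dry W/H / (1 - f), so the scale reads 80% once dry W/H reaches 80 x (1 - f):

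| f | Dry W/H that reads as 80% |
|---|---|
| 5% | 80 x 0.95 = 76.0% |
| 10% | 80 x 0.90 = 72.0% |
| 15% | 80 x 0.85 = 68.0% |

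Under the Inclusion criteria such a child is eligible on oedema alone and meets the endpoint at entry. An oedematous child whose dry W/H is already 80% or more meets it too, whatever f is.

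**2. The two entry rules side by side.** The Inclusion criteria accept either sign. The final-enrolment text requires the Z-score cut-off after rehydration. Suppose the latter applies to every child, and assume that a Z-score of -3 is roughly 70% of the median (a figure not in the documents). Then scale W/H at enrolment is well below 80%, and few or no children start at the endpoint. Fluid still counts towards the crossing for as long as oedema persists: by the table, the scale shows 80% at a dry W/H of 76-68%.

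**3. Rate of weight gain, if counted from admission weight.** Let g be true tissue gain per kg dry weight per day and T the days observed, with all oedema lost by day T. Apparent gain = [(1 - f)(1 + gT/1000) - 1] / T x 1000 g/kg/day. Take g = 10, and T = 14 because daily dosing continues for 14 days after enrolment; T = 7 is shown for contrast.

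| f | T = 14 | T = 7 |
|---|---|---|
| 5% | (0.95 x 1.14 - 1)/14 x 1000 = 5.9 | (0.95 x 1.07 - 1)/7 x 1000 = 2.4 |
| 10% | (0.90 x 1.14 - 1)/14 x 1000 = 1.9 | (0.90 x 1.07 - 1)/7 x 1000 = -5.3 |
| 15% | (0.85 x 1.14 - 1)/14 x 1000 = -2.2 | (0.85 x 1.07 - 1)/7 x 1000 = -12.9 |

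Every entry falls below 10. The sign depends on the window: over 14 days the result is negative only when f exceeds 1 - 1/1.14, about 12%.

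**4. Between arms.** Over a window that outlasts clearance in both arms, fast and slow clearers lose the same total fluid, so speed of clearance does not change net gain. A difference between arms needs either an imbalance in oedema or a window that ends before clearance is complete in one arm.

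**The case against.** A reader might infer that weight gain is certainly taken from raw admission weight. The documents do not say so. Scale weight is the only weight described, but the baseline is left open, a distinct nutritional rehabilitation phase is mentioned, and an analysis plan that is not shown may define the start. On weight gain the point is therefore conditional.

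The 80% endpoint is different: the protocol itself defines it, without an oedema condition. The conflict between the entry rules does limit how often it could be met at entry, and that objection stands until they are reconciled.

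A stronger reading is also tempting: that these outcomes would run in the wrong direction, showing faster oedema loss on low dose as worse gain, or fluid retention on high dose as better gain. The Background does say "This free form of vitamin A perhaps affects sodium and water metabolism", but that sentence concerns pseudotumor cerebri, not peripheral oedema or body weight. The subgroup result in oedematous children that the Background cites concerns deaths. No passage says that either dose changes oedema clearance. Randomisation balances oedema on average, so without such a difference the effect is noise and misclassification.

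Finally, the fluid fraction is assumed and the oedematous share unknown, so no effect on the trial comparison can be calculated.

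**Conclusion.** The point holds for the 80% endpoint as written: with entry on oedema alone, a child can be scored as rehabilitated at or near entry while still severely malnourished by the entry criterion. With fluid assumed at 5-15% of weight, this happens from a dry W/H of 76-68% upwards. Day-0 achievement depends on the Inclusion criteria governing enrolment. If the Z-score rule governs, what remains is an earlier crossing while oedema persists.

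For weight gain the point holds only if gain is counted from admission weight. A true 10 g/kg/day then reads about 5.9 to -2.2 over 14 days, which misclassifies oedematous children against the threshold and adds noise. A bias between arms, or a reversed direction, is not supported by the documents.

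Two of the six listed secondary outcomes are affected; the primary outcomes and the sample size are not. This should be corrected, but it does not threaten the trial's main conclusion.

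**What to change.** 1. Define time to nutritional rehabilitation as the first day with W/H of 80% or more and no bipedal oedema. Weight is already taken every morning and presence of oedema is already recorded, so this costs wording only, provided the record form captures oedema at each daily assessment.
2. Reconcile the Inclusion criteria with the final-enrolment text, so that it is clear whether a child can enter on oedema without meeting the Z-score cut-off.
3. State the baseline and window for rate of weight gain, and report it by baseline oedema status.
4. Add gain from the first oedema-free weight as a supportive analysis, not as the main definition. That baseline is set after randomisation and could itself be affected by treatment. It excludes children who die or leave before oedema clears, and it shortens the observation window in oedematous children. If the minimum weight were used as the start, later gain would also be inflated in those children.

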**Data Analysis**

Describe plans for data analysis. Indicate whether data will be analyzed by the investigators themselves or by other professionals. Specify what statistical software packages will be used and if the study is blinded, when the code will be opened. For clinical trials, indicate if interim data analysis will be required to monitor further progress of the study. **(TYPE WITHIN THE PROVIDED SPACE).**

**Data Analysis:**

Data will be entered onto personal computer using SPSS statistical package and statistical analyses will be performed using the same program, and z- scores will be determined using Epi Info 2001. Normally distributed continuous variables will be compared by t-test for normally distributed data and Mann Whitney U test will be used for data that are not normally distributed. Time to recovery would be compared by log rank test (Kaplan Mayer survival analysis). Two by two tables will be constructed to relate the findings of discrete variable such as chest X-ray findings of pneumonia (present or absent) and Fisher’s exact test would be performed where indicated. Statistical significance will be set at 5% level.

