About half of the absorbed vitamin A is oxidized and excreted in the feces and urine, and the remainder is stored in the liver as retinol ester. It is released into the plasma for transportation to peripheral tissues after binding with specific protein known as retinol binding protein (RBP). Protein deficiency in severe malnutrition reduces the hepatic synthesis of RBP [13], [14], which is the likely reason for low serum retinol level observed in such children [15-17]. Infectious diseases such as diarrhoea, and acute lower respiratory infections including pneumonia are common in malnourished children, which worsen the vitamin A deficiency state [18]. Acute infections are also associated with acute phase response and a transient decrease in serum retinol level [19]. This is due to reduced transcription of messenger RNA for RBP,resulting in decreased release of RBP from the liver into theblood [20] [21]. It is likely that liver utilizes all of its available resources for rapid synthesis of proteins that are required for the host defense in acute infection, thereby limiting the synthesis of less important ones such as RBP. In severe infection the increased urinary loss of retinol contributes to the lower serum retinol concentration [22]. Thus the utilization of vitamin A in the peripheral tissue is adversely affected in systemic infections and protein- energy malnutrition leading to development of features of vitamin A deficiency.

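### Serum retinol and RBP: the named tests do not adjust for the admission value the trial already collects, so the comparison is valid but less precise than it could be

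*Protocol*

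**What the plan says.** The Data Analysis section of the protocol gives one general rule for continuous variables: "Normally distributed continuous variables will be compared by t-test for normally distributed data and Mann Whitney U test" for those that are not normal. It adds "Time to recovery would be compared by log rank test (Kaplan Mayer survival analysis"), two-by-two tables with Fisher's exact test where indicated, and "Statistical significance will be set at 5% level". Neither this section nor any other names a regression model, ANCOVA or a covariate. It does not mention retinol or RBP by name.

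The third secondary aim under Specific Aims is to compare "Serum retinol and retinol binding protein (RBP) levels on admission, day 3 and on day 15". The Secondary outcomes list is shorter: "Serum retinol and RBP on admission and on day 15". Under Laboratory assays, after describing the admission-day blood tests (which include C-reactive protein, CRP), the protocol states: "Serum retinol and RBP will also be measured on study day-3 and 15".

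Two places time the first sample differently. The Project Summary puts it before randomization. The Laboratory assays section puts it after randomization, on the day of admission, and does not say whether it comes before or after the first study capsule.

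**The concern.** Retinol and RBP are the only outcomes that show whether the large initial dose changes circulating vitamin A. Each child supplies an admission value of the same analyte, and that value usually carries information about the later ones. A two-group test on the follow-up value leaves this information unused, and chance differences between arms at admission pass uncorrected into the estimate. At stake is the precision of a secondary, explanatory comparison. The validity of the trial and its primary result are not in question.

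**Working it through.** **The plan's own figure.** The only sample-size calculation is for the binary clinical success outcome, with 70% against 85%: (70×30 + 85×15) / 15² × 7.84 = 3375 / 225 × 7.84 = 117.6, so 118 per arm. This agrees with the Sample size section, which raises it to 130 per arm (260 in all) for about 10% dropout. No calculation is given for retinol or RBP, so the steps below use 118 evaluable children per arm as a working number.

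**Inputs not in the documents.** The standard deviation (SD) of retinol or RBP and the correlation ρ between admission and follow-up values. Results are therefore in SD units, with ρ assumed between 0.1 and 0.7.

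**Step 1: t-test on the follow-up value.** The difference detectable with 80% power at two-sided 5% is (1.96 + 0.84) × √(2/118) = 0.365 SD.

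**Step 2: ANCOVA on the admission value.** The variance is multiplied by 1 − ρ². Power is for the same 0.365 SD difference. The last column is the number per arm at which ANCOVA matches the precision of the t-test with 118.

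| Assumed ρ | Variance remaining | Variance removed | Power | Matching n per arm |
|---|---|---|---|---|
| 0.1 | 0.99 | 1% | 80.4% | 117 |
| 0.3 | 0.91 | 9% | 83.6% | 108 |
| 0.5 | 0.75 | 25% | 89.9% | 89 |
| 0.7 | 0.51 | 49% | 97.5% | 61 |

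**Step 3: if the t-test were on change from admission.** The Data Analysis section does not say which variable is tested. With equal variances at the two times, the variance of change is 2(1 − ρ) relative to the follow-up value alone: 1.4 at ρ = 0.3, 1.0 at 0.5 and 0.6 at 0.7. The ratio of ANCOVA to change is (1 − ρ²) / [2(1 − ρ)] = (1 + ρ)/2. ANCOVA then saves 35% of the variance at ρ = 0.3, 25% at 0.5 and 15% at 0.7. It gains on either reading.

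**Step 4: why the timing of the first sample matters.** The ANCOVA estimate is the difference in follow-up means minus b times the difference in baseline means, where b is the fitted slope. If the baseline sample precedes the capsule, the second difference is zero on average and the estimate is unbiased. If the sample follows the capsule and the large dose has already shifted it by δ, the estimate is off by about −bδ, which could remove part of the effect being measured. Sampling before randomization, as in the Project Summary, necessarily means before the capsule. Sampling after randomization on the admission day, as under Laboratory assays, could fall on either side of it.

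**The case against.** The strongest reply is that nothing here is an error. The named tests are valid under randomization, and their error rate already allows for chance imbalance. The Data Analysis section is a short general list, and a statistical analysis plan, not shown here, could specify adjustment. All of this stands, and it limits the weight of the point. It does not remove it, because the protocol does name a method for continuous variables, and a better one is available from data already collected.

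A reader might infer four stronger things that the documents do not support:

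- **That the baseline is ignored.** The text does not exclude a t-test on change from admission, which uses the baseline, though less efficiently (Step 3).
- **That admission retinol and CRP must explain much of the later spread.** The Background says "Acute infections are also associated with acute phase response and a transient decrease in serum retinol level". No correlation follows from that. If admission values are temporarily depressed and later recover, the correlation with day 15 could be weak, and at ρ = 0.1 the gain is 1%.
- **That every continuous outcome is affected.** Time to recovery has a log-rank test. Duration of illness and time to nutritional rehabilitation have no admission value of the same variable. Rate of weight gain is already measured from the starting weight.
- **That adjustment also deals with missing day-15 samples.** ANCOVA on complete cases does not recover them.

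**Conclusion.** The point holds for serum retinol and RBP only, as a minor gain in efficiency on a secondary outcome. The direction is secure: with a pre-dose baseline and about 118 children per arm, ANCOVA is at least as precise as a t-test on either the follow-up value or the change. The size cannot be fixed from the documents. It runs from negligible (1% of variance at ρ = 0.1) to large (49% at ρ = 0.7), all on assumed correlations. The figures are for a t-test and a linear baseline relation with a common slope, and they apply only approximately where Mann-Whitney would be used. The primary outcomes and the 118, 130 and 260 are unchanged.

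The conflict over when the first sample is taken has to be settled before the adjustment is adopted.

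**What to change.** 1. In Data Analysis, add that day-3 and day-15 retinol and RBP will each be compared between arms by ANCOVA, or by one repeated-measures model covering both days, adjusted for the pre-dose admission value of the same analyte. Use the log scale if the values are skewed. Admission CRP may be added as an optional covariate. Report the adjusted difference, or the adjusted ratio on the log scale, with a 95% confidence interval.
2. Reconcile the Project Summary with Laboratory assays on when the first sample is drawn, and state that the baseline retinol and RBP sample is taken before the first study capsule.
3. Align the Secondary outcomes list, which omits day 3, with Specific Aims.

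The cost is wording, plus a clear instruction on the order of blood draw and capsule on the first day. No new visit, assay or child is needed, and the sample size stays as it is.
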